Against this background, the POSITION project aims to study the cognitive mechanisms involved in body awareness, both as a risk factor in fall injury, and as a target for a prevention strategy that aims to reduce the injury rate by improving postural control.

This research project was prompted by epidemiological observations carried out during the French Marine Commando Selection Course (STAC). Medical unfitness due to incapacity is the leading cause of failure (70%). Acute trauma is the principal pathology (60%), typically involving the lower limbs (Bertrand, 2016; Longin, 2015; Morinière, 2013). A review of the circumstances surrounding the trauma highlighted that a fall due to a loss of balance was the cause in 90% of cases (Bertrand, 2016). These data suggest that postural balance could play a role in the injuries encountered during the STAC. The activities that candidates must undertake require them to have extremely good postural balance: trainees carry heavy loads (a combat bag and a weapon, weighing 15 kg) for prolonged periods, and complete extreme challenges that are run at-height in all weather conditions. Epidemiological data collected during the course show that the leading activity resulting in trauma is the ‘jungle’ challenge, which involves overcoming obstacles up to 5 meters high with no safety net (Morinière, 2013). Moreover, preliminary (unpublished) epidemiological data collected from other military units (the National Gendarmerie, the 1st Marine Infantry Parachute Regiment, the 13th Parachute Dragoon Regiment, the 10th Air Parachute Commando, and the Fusiliers Marins [Navy Riflemen] School, Paris Fire Brigade) seem to confirm the high rate of trauma linked to a loss of postural balance during physical activities.

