# EVALUATION CRITERIA

## Primary endpoint

The primary endpoint will be the rate of fall injuries following a loss of balance in each of the two groups (POTs *vs.* active control).

A fall injury will be recorded by the medic responsible for providing healthcare during the selection course. The injured participant will be required to attend an additional follow-up visit on the same day after the initial medical consultation.

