### End-of-study visit

Participant follow-up will end either: (*i*) on the day following the last session of the POTs or the active control intervention; or (*ii*) the day they leave the course (for whatever reason), if this occurs before the end of the intervention (POTs or active control).

A posturography measurement will be performed by the military medic, or one of his or her assistants, and the participant will complete questionnaires measuring postural awareness (the Postural Awareness Scale) and perceived stress (Cohen’s Perceived Stress). Finally, a 4 ml saliva sample will be collected.

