## End of the study

### Discontinuation criteria for a participant

Participation will end:

- After the last session of the intervention (POTs or active control),
- On leaving the course (for whatever reason) if this occurs before the end of the intervention.

It will not be possible for a participant who leaves to re-join the program at a later date.

There are no exclusion criteria in the protocol.

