**Analysis of the main objective**

The effect of the intervention (POTs *vs.* active control) on the rate of fall injuries will be evaluated using a comparative survival analysis (the Cox model, with clinical variables as potential confounders). Survival curves for POTs and active control groups will be compared using the log-rank test.

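### The primary endpoint is a proportion injured per group, but the named analyses give no interval estimate of that difference and do not treat leaving the course uninjured as a competing event

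*Protocol*

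**What the plan says.** Protocol, Primary endpoint: "The primary endpoint will be the rate of fall injuries following a loss of balance in each of the two groups". The section on the number of subjects treats this rate as a proportion: 50% under active control, 35% under POTs, two-sided 0.05, power 0.80, 10% drop-out, 200 per group.

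Protocol, Analysis of the main objective: the intervention effect is evaluated by a Cox model adjusted for clinical variables, and "Survival curves for POTs and active control groups will be compared using the log-rank test". The fourth secondary objective uses the same two methods.

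Protocol, End-of-study visit: follow-up ends the day after the last session or on "the day they leave the course (for whatever reason), if this occurs before the end of the intervention". The discontinuation criteria repeat this for participation ("On leaving the course (for whatever reason) if this occurs before the end of the intervention") and add: "It will not be possible for a participant who leaves to re-join the program at a later date".

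Protocol, Statistical methods: a flow chart is planned, and all collected variables are described by group, categorical ones as frequencies and percentages.

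Protocol, Randomization: allocation is by calendar year, with active control in year Y and POTs in year Y+1.

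**The concern.** A participant who leaves uninjured can no longer have a fall injury on that course, and cannot return. Leaving uninjured therefore removes the possibility of the event; it does more than end observation. A survival curve that censors such participants answers what would happen if nobody left, whereas the endpoint and the sample size concern the share of participants who are injured.

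Two things are at stake. First, a reader who takes one minus the curve as the injury rate would get a figure that is too high in both groups. Second, if leaving differs between groups, the injured proportions can differ while the injury hazards are equal, or the reverse. The arms run in successive years without randomization, so any year-to-year change in attrition falls entirely on the group comparison. Several POTs sessions (Appendix 2) also address motivation, self-confidence and stress, which could plausibly affect staying on the course.

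**Working it through.** **Inputs from the Protocol.** Injured proportions 50% and 35%; alpha 0.05 two-sided; power 0.80; drop-out 10%; intervention three weeks. **Not given:** the proportion who leave without a fall injury, overall or by group. It is varied below as an assumption.

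**1. The plan's own figure.** The two-proportion formula with pooled variance under the null is n = [1.960·√(2·0.425·0.575) + 0.842·√(0.50·0.50 + 0.35·0.65)]² / 0.15², which gives 170 per group, or 183 with continuity correction. Allowing for 10% drop-out, 183/0.9 gives 204 and 183·1.1 gives 202. Without the correction, 170/0.9 gives 189. The stated 200 is thus consistent with a comparison of two proportions, which confirms the scale on which the trial was designed.

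**2. Size of the gap between curve and proportion.** Assume constant hazards over the period: *a* for fall injury and *b* for leaving uninjured. Let F be the share injured and G the share leaving uninjured.
- Total hazard: a + b = −ln(1 − F − G)
- Fall hazard: a = (a + b)·F/(F + G)
- One minus the curve, leavers censored: 1 − exp(−a)

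Example with F = 0.50, G = 0.10: a + b = −ln(0.40) = 0.916; a = 0.916·0.5/0.6 = 0.764; 1 − exp(−0.764) = 53.4%.

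| Leaving uninjured (assumed, both groups) | Curve when 50% are injured | Curve when 35% are injured | Apparent difference (true 15 points) |
|---|---|---|---|
| 5% | 51.6% | 36.0% | 15.6 |
| 10% | 53.4% | 37.2% | 16.2 |
| 20% | 57.7% | 39.8% | 17.9 |
| 30% | 63.4% | 43.2% | 20.2 |

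The 10% row uses the Protocol's drop-out figure and assumes that all drop-outs are uninjured leavers. The 20% and 30% rows are illustrations only.

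**3. Unequal leaving at a hazard ratio of 1.** The share injured is a/(a + b)·[1 − exp(−(a + b))]. Take the same injury hazard in both groups, a = ln 2 = 0.693, so that both curves read 50%. Let the probability of leaving, if nobody were injured, be 10% in one group (b = 0.105) and 30% in the other (b = 0.357).
- 10% leaving: 0.693/0.799·(1 − 0.45) = 47.7% injured
- 30% leaving: 0.693/1.050·(1 − 0.65) = 42.9% injured

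The proportions differ by 4.8 points, about a third of the 15-point design effect, with identical curves. The sign depends on which group leaves more. A second illustration starts from 50% injured and 30% leaving (a = 1.006, b = 0.604) and halves the leaving hazard to 0.302. The share injured becomes 56.1% with the fall hazard unchanged. Both leaving patterns are assumed.

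**The case against.** A reader might infer that the Protocol will report inflated injury rates. It does not say so. The curves are only to be compared by log-rank test, and no sentence says that group rates will be read from them. Censoring of leavers is likewise inferred from standard practice; the Protocol does not state it.

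A reader might also infer that the primary test is invalid. It is not. Cox and log-rank analyses with leavers censored compare cause-specific injury hazards validly. For a question about preventing falls during activity, not counting longer exposure as harm is defensible.

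Nor is an effect on leaving hidden. Leaving dates are collected (mentioned under the fourth secondary endpoint), a flow chart is planned, and variables are described by group. The crude injured percentage is available from that description. If everyone is followed to leaving or to the end of the intervention, it equals the cumulative incidence at that point; only withdrawal of consent could separate the two.

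Finally, leaving rates above 10%, and any difference by arm, have no figure behind them. The background states that 70% of failures on the marine commando course are medical. That is a share of failures, not a rate per candidate, and the text sets that course apart from the other units, which match the study's six. Some of the detail could also sit in an analysis plan that is not shown.

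All of this stands, and it limits the point. It does not supply an interval for the difference on the endpoint's own scale, or a planned comparison of leaving between non-concurrent arms.

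**Conclusion.** The point holds as a modest improvement to the analysis and does not fault the primary test. Endpoint and sample size are proportions injured; the named inferential methods address hazards and survival curves; and the Protocol's own follow-up rule makes uninjured leaving a competing event. If leavers are censored, one minus the curve overstates the injured share by about 2 to 3 points at 10% uninjured leaving, and by roughly 5 to 13 points at an assumed 20% to 30%. Unequal leaving of 10% versus 30% would move the injured proportions about 5 points apart at a hazard ratio of 1. These sizes rest on constant hazards and on leaving rates that the Protocol does not give. The direction of the overstatement needs only that some participants leave uninjured and are censored.

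**What to change.** In the analysis of the main objective:
- Keep the cause-specific Cox model as the test, and state that participants who leave uninjured are censored in it on the day of leaving.
- Replace the survival curves as the group display with the cumulative incidence of first fall injury (Aalen-Johansen), with leaving without a fall injury as the competing event.
- Report the risk difference at the end of the three weeks with a 95% CI.
- Report the cumulative incidence of leaving uninjured by group.

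Apply the same to the fourth secondary objective, as far as it includes participants who leave before the course ends.

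The inputs are the fall-injury record and the date of leaving. The reason for leaving is not required. The leaving date is mentioned only under the fourth secondary endpoint, so the wording should make clear that it is also used for the primary analysis. The cost is a change of wording and slightly more analysis work, with no new data and no change in sample size.

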**Analysis of secondary objectives**

For the first secondary objective, the effect of the POTs intervention on postural awareness will be evaluated by comparing the following for the POTs group: (*i*) scores on the Postural Awareness Scale at the six measurement times (repeated measures ANOVA), and (*ii*) posturography measurements pre- and post-intervention (paired samples comparison of means).

For the second secondary objective, the effect of the POTs intervention on the psychobiological stress response will be evaluated by comparing the following measures for the POTs group at all six measurement times: (*i*) scores on Cohen’s Perceived Stress Questionnaire (repeated measures ANOVA), and (*ii*) biological stress variables (paired samples comparison of means).

For the third secondary objective, machine learning will be used to evaluate the accuracy of the predictive model of the risk of fall injury using the following calculation:

|  | $\text{Accuracy=}\frac{\text{True }\text{Fall-related injury }\text{participants + True }\text{Non-fall }\text{participants}}{\text{Total number of participants}}$ |  |
| --- | --- | --- |

where N_prediction of trauma_ is the number of participants for whom the machine learning model predicts the occurrence of a fall injury and who do, in fact, suffer a fall injury during the selection course; N_prediction of_ _good health_ is the number of participants for whom the model predicts the non-occurrence of a fall injury and who do not, in fact, suffer a fall injury during the selection course; and N_total_ is the total number of participants included in the study.

For the fourth secondary objective, the long-term effectiveness of the POTs intervention in preventing fall injuries between the end of the study and the end of the selection course will be evaluated using a comparative survival analysis (the Cox model). Survival curves for POTs and active control groups will be compared using the log-rank test.

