| Schedule | The study will consist of the following visits:   - 1 inclusion visit: inclusion interview and written consent - 1 initial assessment visit: self-report questionnaires (medico-biographical, postural awareness (Postural Awareness Scale) and stress (Cohen’s Perceived Stress Scale), clinical and paraclinical posture measurements and saliva collection. - 4 follow-up visits carried out at the start of the POT or active control sessions, consisting of: self-report questionnaires (postural awareness and perceived stress), - there will be 1 additional visit for participants who suffer a fall-related trauma during the course. The participant will complete questionnaires measuring postural awareness and perceived stress, and a posturography measurement will be performed. - 1 end-of-study visit will take place on the day following the last session of the POT or the active control, or on the day of the fall injury if it occurs before the end of the POT or active control intervention. This visit will include: paraclinical measurement of posture, self-report questionnaires (postural awareness and perceived stress) and saliva collection. |
| Number of subjects | The sample should include 200 participants in each of the two groups (POT and active control), making a total of 400 participants. |

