| Statistical analysis | For the primary objective, the effect of the intervention (POT *vs.* active control) on the rate of fall-related injuries will be evaluated using a comparative survival analysis (the Cox model, with clinical variables as potential confounders).  For the first secondary objective, the effect of the POT intervention on postural awareness will be evaluated by comparing the following for the POT group: (*i*) scores on the Postural Awareness Scale at the six measurement times (repeated measures ANOVA), and (*ii*) posturography measurements pre- and post-intervention (paired samples comparison of means).  For the second secondary objective, the effect of the POT intervention on the psychobiological stress response will be evaluated by comparing the following measures for the POT group at six measurement times: (*i*) scores on Cohen’s Perceived Stress Questionnaire (repeated measures ANOVA), and (*ii*) biological stress variables (paired samples comparison of means).  For the third secondary objective, machine learning will be used to evaluate the accuracy of the predictive model of the risk of fall injury based on the accuracy on the prediction.  For the fourth secondary objective, the long-term effectiveness of the POT intervention in preventing fall-related injuries, between the end of the study and the end of the selection course will be evaluated using a comparative survival analysis (the Cox model). |
| Study duration | Duration of inclusion: 24 months  Duration of the intervention: 3 weeks  Duration of each participant’s participation: 4 weeks  Total study time: 25 months |

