## Secondary objectives

The study has 4 secondary objectives:

1. The first is to test the mechanistic hypothesis that POTs reduce the risk of fall-related injury by improving postural awareness.
2. The second is to test the mechanistic hypothesis that POTs reduce the risk of fall injury by decreasing the intensity of the psychobiological stress response during physical activities in the military context.
3. The third is to use machine learning techniques to develop a predictive model of the risk of fall injury, based on a clinical test (BESS) and paraclinical (posturography) measurements taken before physical activities begin.
4. The fourth is to evaluate the persistence over time of the effectiveness of a POT intervention in reducing the risk of fall injury. The assessment will be based on participants who continue to engage in physical activities after the end-of-study visit (and who complete the selection course); the analysis will compare the rate of fall injuries for POTs and active control groups.

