### Follow-up visits

A follow-up visit will be carried out just before each session of the POTs and active control interventions (the schedule for which is shown in Figure 4). During the follow-up visit, the participant will complete self-report questionnaires measuring postural awareness (the Postural Awareness Scale) and perceived stress (Cohen’s Perceived Stress).

Participants who suffer a fall trauma during the course will attend an additional follow-up visit, which will take place on the day of the injury. The military medic, or one of his or her assistants, will collect medical information relating to the trauma, and carry out a posturography measurement. The participant will then complete questionnaires measuring postural awareness (the Postural Awareness Scale) and perceived stress (Cohen’s Perceived Stress).

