### Biological parameters

A saliva sample will be collected during the initial evaluation visit, and the end-of-study visit (2 x 2 ml at each visit). These samples will be used to monitor markers of the corticotropic axis (cortisol and DHEA), and the autonomic nervous system (alpha-amylase and chromogranin).

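### Secondary objectives 1 and 2 are tested only by change over time within the POTs group, so an effect of POTs cannot be separated from the selection course, although the same measures are collected in the control group

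*Protocol*

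**What the plan says.** Both objectives are causal. The first is to "test the mechanistic hypothesis that POTs reduce the risk of fall-related injury by improving postural awareness"; the second makes the parallel claim for the psychobiological stress response (Protocol, Secondary objectives).

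The planned analyses use one arm. In Analysis of secondary objectives, "the effect of the POTs intervention on postural awareness will be evaluated by comparing the following for the POTs group": a repeated-measures ANOVA of the Postural Awareness Scale and a paired pre/post comparison of posturography. For stress, the effect "will be evaluated by comparing the following measures for the POTs group at all six measurement times", with a repeated-measures ANOVA of the perceived stress score and a paired comparison of the salivary markers. The Research Summary repeats the restriction: "the effect of the POT intervention on postural awareness will be evaluated by comparing the following for the POT group". The primary and fourth objectives, by contrast, compare POTs with active control. For the control arm, Statistical methods plans only description of the awareness, stress, posturography and saliva data.

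The control data exist. "A follow-up visit will be carried out just before each session of the POTs and active control interventions" The End-of-study visit section takes posturography, both questionnaires and saliva in both arms. The caption of Figure 4 says that both years follow one schedule and differ only in session content. Biological Sample Collection counts saliva from all 400 subjects at two times.

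The number of measurement times is not consistent. The biological variables fall under the six measurement times, yet "A saliva sample will be collected during the initial evaluation visit, and the end-of-study visit". The Research Summary has "4 follow-up visits carried out at the start of the POT or active control sessions", whereas the Follow-up visits section has one before each session, and The intervention section gives six sessions.

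**The concern.** A test of change over time in a single arm asks whether scores moved, not whether POTs moved them. At least three other things can move them in this setting:

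- **The course itself.** The Scientific Justification says that its physical and psychological challenges activate the stress response. The Research Summary adds that high stress could degrade postural balance.
- **Repeated testing.** The same two questionnaires are completed at least six times in about three weeks, and posturography is repeated.
- **Early leaving.** The end-of-study measures are brought forward to the day a participant leaves the course (End-of-study visit) or the day of a fall injury (Research Summary). Some post-intervention values will therefore reflect a fresh injury.

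The error can go either way. A favourable shift common to both arms would look like a POTs effect, and an unfavourable one could cancel a real POTs benefit. In neither case does the planned test answer the objective, and the control data that would help are left out of it.

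**Working it through.** **The plan's own figure.** The protocol gives no sample size, SD or expected change for objectives 1 and 2. Its only sample-size figure is 200 per group for the primary endpoint (50% versus 35%, two-sided 0.05, power 0.80, 10% drop-out). That reproduces: with continuity correction 183 per group, then 183/0.9 = 204 or 183 × 1.1 = 202. Without the correction it is 170, then 170/0.9 = 189. It is used here only for the evaluable number, 200 × 0.9 = 180.

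**Assumptions (not in the documents).** A shift common to both arms of 0.1, 0.2 or 0.3 SD of the score; pre/post correlation 0.6; 180 evaluable in the POTs arm; no POTs effect.

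**Case 1: course shift, no POTs effect, planned paired test.**

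- SD of the change = √(2 × (1 − 0.6)) = 0.894 SD.
- Non-centrality = shift / 0.894 × √180, with √180 = 13.42.
- Probability of significance = P(|Z + non-centrality| > 1.96).

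| Common shift (SD of score) | Non-centrality | Planned test significant |
|---|---|---|
| 0.1 | 1.5 | 32% |
| 0.2 | 3.0 | 85% |
| 0.3 | 4.5 | 99% |

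Nearly all of these results lie in the direction of the shift. If the course worsens the score by 0.2 SD, the chance of a significant result in favour of POTs is P(Z > 1.96 + 3.0), which is practically zero.

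The figure depends on the assumed correlation. At 0.2 SD:

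- correlation 0.4: SD of change 1.095, non-centrality 2.45, 69%;
- correlation 0.8: SD of change 0.632, non-centrality 4.24, 99%.

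A between-arm test of change keeps its 5% error whatever the common shift. A simulation of 5,000 trials with 180 per arm gave 4.8% to 5.2% for shifts of 0 to 0.5 SD of change.

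**Case 2: a real POTs benefit cancelled by the course.** This case is scaled in SDs of the change: benefit 0.3, course deterioration 0.3. At correlation 0.6 that is 0.3 × 0.894 = 0.27 SD of the score.

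- Planned test: net change in the POTs arm = 0.3 − 0.3 = 0, so it is significant only at its 5% error rate (4.5% in the simulation).
- Between-arm test: non-centrality = 0.3 × √(180/2) = 2.85 and P(Z > 1.96 − 2.85) = 81% (81.5% in the simulation).

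**Measurement times.** Baseline + 4 follow-ups + end = 6. Baseline + 6 pre-session visits + end = 8. Saliva: baseline + end = 2.

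**The case against.** **Direction.** A reader might infer that any course-driven change will be credited to POTs, and might read the 85% as a false-benefit rate. The documents do not support that. The hypotheses are directional, and the protocol expects the course to raise stress and perhaps impair balance. A significant worsening would not be claimed as a benefit. The percentages are two-sided rejections, and they are false-benefit rates only if the course improves the score. On the protocol's own premises, masking is the likelier error for stress and balance.

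**Inputs.** The shift, the correlation and the 180 are assumptions, and the arithmetic covers the paired test only. The questionnaire ANOVA was not evaluated numerically. It has the same one-arm weakness, but these percentages do not carry over to it.

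**Use of the control arm.** It would be too strong to say that the control is unused. It serves the primary and fourth objectives, and every variable is described by group. What is missing is a between-arm test for objectives 1 and 2.

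**Limits of the remedy.** Control runs in year Y and POTs in year Y+1, in that order in every unit (Randomization), so adjustment for unit and baseline cannot remove a calendar-year difference. If POTs reduce injury as assumed, from 50% to 35%, early leaving will differ between arms. The control sessions also cover sensory channels, attention and mental imagery (Appendix 2), so the contrast is with an active comparator that overlaps POTs content. All of this stands and limits interpretation, but it does not justify a one-arm test.

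**A separate analysis plan.** One may exist, but the protocol names the analysis group and the tests in two places, so this is not detail left open.

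**Visit counts.** The six measurement times for saliva are loose lead-in wording: the same sentence names a paired comparison, and other sections clearly give two samples. Four versus six follow-ups is a true conflict, though Figure 4 and Table 1, which may settle it, are not visible here. Both are reconciliation items and do not carry the main point.

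**Conclusion.** The point holds. As written, the analyses of objectives 1 and 2 cannot distinguish an effect of POTs from the effects of the course, repeated testing and early leaving, and the error can run in either direction. On the stated assumptions, a modest common shift of 0.2 SD makes the paired test significant in 85% of trials with no POTs effect (32% at 0.1 SD, 99% at 0.3 SD), always essentially in the direction of the shift. A benefit exactly offset by the course would be found about 5% of the time, against about 81% between arms. These figures illustrate the size of the problem and do not predict this trial.

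Even a between-arm result would show only an effect on awareness or stress. No planned analysis links either to injury, so the claim that POTs reduce injury through them would remain untested.

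Severity: should be fixed. These are secondary objectives and the primary comparison is not affected.

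**What to change.** 1. Make the test for objectives 1 and 2 a comparison between arms.
   - Postural awareness and perceived stress: a mixed model over all measurement times in both arms, with an arm-by-time contrast as the test, adjusted for baseline and unit.
   - Posturography and salivary markers: the end-of-study value compared between arms, adjusted for its baseline and unit.
2. State that this removes course and practice effects common to both arms, but neither the calendar-year confounding of the sequential design nor differential early leaving.
3. Put any analysis linking awareness or stress to injury in a separate exploratory model. Adding these scores to the primary Cox model would condition the treatment effect on a supposed mediator and change what the primary analysis estimates. Without such a model, limit the conclusion to an effect on awareness or stress.
4. Change the saliva wording from six measurement times to two, and reconcile four follow-up visits (Research Summary; visit codes in Biological Sample Collection) with a visit before each of six sessions (The intervention; Follow-up visits).

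Cost: no new data or visits, since the control measures are already collected. The change is to analysis wording in two sections. If the sponsor classes it as substantial, the Protocol amendment section requires a written amendment and a favourable opinion from the Institutional Review Board. It should be made before the data are analysed.
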